### **VIII-2. Maintenance of group comparability**

The standard of care for COVID-19 is evolving rapidly. We will take specific measures to ensure that groups the standard of care used in participating patients remain comparable in both arms over the inclusion period. Whenever necessary, the trial steering committee will provide updated guidelines regarding the standard of care and will strongly recommend that participating centres observe them.

These recommendations may consider the local availability of COVID-19 specific medications such as MoAbs.

The primary endpoint is COVID-19 related hospitalisation or death by day 28. Hospitalisation or the decision to extend a hospitalisation may depend on local practice and availability of health service at the time of hospitalisation. In order to minimise bias on this endpoint, we will set up a three member panel to adjudicate whether hospitalisation or the decision to extend hospitalisation was COVID-related or not. Each member will independently come to a decision on whether the hospitalization was or was not related to COVID-19 using as much information that could be provided such as hospital discharge forms. Classification of whether the hospitalization was due to COVID-19 will be by majority decision of the panel.

Reasonable efforts will be made to keep the panel blinded for the randomisation group while also providing accurate information about the patient. As a general rule, information about the intervention will be removed from the discharge forms when possible, but clinical data about potential transfusion reactions and adverse events will not.

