## I. STUDY PRESENTATION - CONTEXT

The COVIC-19 study is a prospective randomized clinical study evaluating the benefit of COVID-19 convalescent plasma (CCP) with a very high antibody titre administered early, on an outpatient basis, to vulnerable patients to prevent the progression of a COVID-19 disease to a severe form requiring hospitalization. The vulnerable patients concerned by this study are patients with recently diagnosed COVID-19 disease who do not need hospitalisation and who are: at least 70 years old; younger patients with risk factors for severe COVID-19; and patients with primary or secondary immunodeficiency. Patients randomized to the treatment arm will receive 2 units of CCP with high titre anti-SARS-CoV-2 antibody on an outpatient basis within 7 days of the onset of symptoms of COVID-19. Patients in the control group will not receive a specific intervention.

This study is based on growing evidence for the effectiveness of passive immunotherapy, by transfusion of CCP or administration of monoclonal antibodies, as long as treatment is carried out early after the diagnosis of the disease. In a recent randomized clinical trial in Argentina by Libster et al, the administration of CCP less than 3 days after the onset of symptoms of COVID-19 in vulnerable patients halved the risk of developing severe COVID-19 disease compared to a control group (16% after CCP transfusion vs. 31% without transfusion). Similar findings were recently reported in a clinical trial coordinated by the John Hopkins Hospital (USA). A third randomized trial found similar results as well for patients included less than 5 days after symptoms initiation. A 4th study did not confirm this efficacy of CCP, with however inclusion criteria that differed significantly (patients recruited in emergency rooms).

Importantly, a significant antibody dose response was observed. Likewise, the early administration of monoclonal anti-SARS-CoV-2 antibodies in mono- or bitherapy has been associated with a decrease in the frequency of hospitalization for COVID-19 disease.

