Lastly, transient lung-function worsening (transient increased O2 requirement) early after CCP transfusion and without evidence of circulatory overload has been observed in several immunosuppressed patients hospitalized for severe COVID-19 in France (unpublished data). Importantly, such occurrences, always transient, do not prevent a subsequent favourable effect of CCP on the course of COVID-19. The mechanisms involved are currently unknown and could hypothetically result from immune complex formation in airway tissues of severely ill patients unable to clear SARS-CoV-2. It is expected that patients at earlier stage of the disease, and notably in the absence of severe lung disease, will be at lesser risk of such occurrences. Such early transient respiratory worsening has not been reported in the Libster study mentioned earlier as well as other studies involving immunosuppressed patients.

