#### **III-4. Study endpoints**

**The primary endpoint** is the proportion of participants with (1) at least one overnight stay in hospital for progressive COVID-19 symptoms, or (2) who died, by day 28 after randomisation. COVID19 related

hospitalizations will be adjudicated using a three member panel. Each member will independently come to a decision on whether the hospitalization or decision to extend a hospitalisation was or was not related to COVID-19 using as much information that could be provided such as hospital discharge forms but remain blinded for the randomization group. Classification of whether the hospitalization was due to COVID-19 will be by majority decision of the panel.

Secondary outcome measures include core outcomes from the meta-core outcome set (COS) for hospitalised patients (<http://www.comet-initiative.org/Studies/Details/1538>), and the WHO progression scale. There is no COS for patients with COVID-19 managed in the community. Viral outcome measures will enable assessment of mechanism.

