## **IV. STUDY DESIGN**

### **IV-1. Overall design**

COVIC-19 is a multicentre international, randomised, open-label adaptive superiority phase III trial to evaluate the efficacy and safety of COVID-19 convalescent plasma in the treatment of COVID-19. It is conducted in a harmonized approach in different countries in Europe.

The study is randomizing adult COVID-19 patients to one of two arms (1:1 ratio): standard of care or standard of care and very high neutralizing Ab titre convalescent plasma. Randomization will be stratified by centre and by patient cohort. The control group will receive 'standard care' therapy. Neither blinding nor placebo will be used to avoid unnecessary intravenous access.

Standard of care therapy may include anti-SARS-CoV-2 specific medication listed as authorized in a dedicated appendix. Centres should ensure that medications used as standard of care are used similarly for patients in both treatment arms.

Participating patients will be included in 2 cohorts of vulnerable patients (cohort 1: unvaccinated elderly ( $\geq 70$  years) and younger with comorbidities (cohort 1:  $< 70$  with comorbidities), cohort 2: immunosuppressed patients).

All subjects will undergo a series of efficacy and safety assessments, including laboratory assays. Subjects will be assessed at baseline, and at Days 3, 14, 28, 90 and 180.

Nasopharyngeal swabs (NP) or lower respiratory tract samples will be obtained at D1 (pre-treatment), and at D3, D14, D28 and D180 (and monthly in case of positivity until of clearance) for cohort 2 and on the day of hospitalization (if applicable).

Blood samples will be obtained at D1, D14 and D28 and on the day of hospitalization (if applicable).

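### The endpoint panel is declared blinded, but its files may keep transfusion-reaction data that point to the plasma arm, and no efficacy analysis counts all-cause hospitalisation

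*Protocol*

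**What the plan says.** Protocol section III-4 defines the primary endpoint as an overnight hospital stay for progressive COVID-19 symptoms, or death, by day 28. It says that COVID-related "hospitalizations will be adjudicated using a three member panel", and that members decide "using as much information that could be provided such as hospital discharge forms but remain blinded for the randomization group".

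Section VIII-2 describes the same panel as a measure against bias, with a weaker promise: "Reasonable efforts will be made to keep the panel blinded for the randomisation group while also providing accurate information about the patient". Information about the intervention is to be taken out of discharge forms when possible, "but clinical data about potential transfusion reactions and adverse events will not".

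On the comparison itself, section IV-1 says "Neither blinding nor placebo will be used to avoid unnecessary intravenous access", and section I says "Patients in the control group will not receive a specific intervention". Section IX-1-1 lists the expected serious transfusion reactions. They include sudden respiratory worsening, acute lung injury, transfusion-related dyspnoea and fever.

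**The concern.** Treating staff know the arm, so the blinded panel is the main protection of the hospitalisation component. Two things weaken it.

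First, the two sections disagree on whether the panel is blinded. The material that VIII-2 keeps in the file is not neutral. General adverse events occur in both arms and reveal little. A suspected reaction to study plasma can arise only in the plasma arm. It also offers a competing explanation for the very question the panel answers. The same respiratory picture in a control has no such alternative label.

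Second, apart from blinding, an admission truly caused by plasma is not a stay for progressive COVID-19. It therefore does not count against plasma in the primary endpoint. No efficacy analysis listed in sections III-4 or X-3 counts overnight stays from any cause, so a reader could not see how many such stays were set aside in each arm.

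**Working it through.** **Comparing the passages.** III-4: members "but remain blinded for the randomization group". VIII-2: reasonable efforts, with a written exception for potential transfusion reactions. These cannot both describe the panel's files. The conflict lies within the protocol, so it is not a detail left to a later document.

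**Reproducing the plan's figure.** Section X-2 gives 158 per group for 0.30 v 0.15, two-sided alpha 0.05, 90% power:

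(1.96 + 1.2816)² × (0.30×0.70 + 0.15×0.85) / 0.15² = 10.51 × 0.3375 / 0.0225 ≈ 157.6, so 158 (unpooled variance; 161 pooled).

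The figure is reproduced, and the illustration below uses the same test and risks.

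**How many patients.** Section II-5-1 cites severe or serious transfusion-related events in 0 to 1.3% of plasma recipients in four randomised trials. With 170 per arm (X-2), the ceiling is 0.013 × 170 = 2.2 patients. The same section gives lower figures:
- Severe allergic reactions in 16 of 5795 plasma patients in a large inpatient trial: 0.28%, or about 0.5 of 170.
- National haemovigilance, 11.4 grade 3 events per 100,000 plasma units: 340 units × 11.4/100,000 = 0.04 events.

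**Effect on the test if plasma does nothing.** Let r be the share of plasma patients whose only qualifying event is reclassified as not COVID-related. This is an assumption; the protocol gives no such figure. The plasma risk is then pT = pC − r, and the chance of a significant result favouring plasma is

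Φ[(r − 1.96·SE₀)/SE₁], with SE₀ = √(2p̄(1−p̄)/n) and SE₁ = √((pC(1−pC) + pT(1−pT))/n).

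For pC = 0.30, r = 0.013, n = 170: p̄ = 0.2935 and SE₀ ≈ SE₁ ≈ 0.0494, so (0.013 − 0.0968)/0.0494 ≈ −1.70, which gives 4.5%. The opposite tail is 1.3%, so the two-sided rate is 5.8%.

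| Control risk | n per arm | r = 0 | r = 0.3% | r = 1.3% | Apparent RR at 1.3% |
|---|---|---|---|---|---|
| 30% (planned) | 170 | 2.5% | 2.9% | 4.5% | 0.96 |
| 30% | 510 (maximum) | 2.5% | 3.2% | 6.6% | 0.96 |
| 6.3% | 170 | 2.5% | 3.3% | 7.5% | 0.79 |
| 6.3% | 510 | 2.5% | 3.9% | 14.4% | 0.79 |

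The 6.3% risk is the control rate in the large outpatient plasma trial described in section II-3-3. At that rate and 170 per arm there are only about 11 events per arm, so the normal approximation is rough. The 510 is half of the 1020 maximum per cohort.

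**Against the effect sizes.** 1.3 points is 1.3/15 = 9% of the planned difference, and 1.3/3.4 = 38% of the difference in that outpatient trial.

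**The case against.** The sentence in VIII-2 can be read kindly: mentions of plasma are removed, and only clinical signs such as fever, rash or dyspnoea stay. On that reading the practice is close to the remedy proposed here. The text does not settle it, because it names potential transfusion reactions as what is retained. The kind reading is a reason to clarify the wording, not to leave it. An immunocompromised control could also have an unrelated transfusion, but that would be incidental.

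The cause-specific endpoint is a deliberate choice. Section II-3-3 places this trial close to one with a disease-specific outcome and contrasts it with one that counted admission for any reason. This stands. A fully blinded panel would also exclude a clear transfusion-reaction admission, so that loss comes from the definition and not from unmasking.

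There are partial safeguards. Death counts whatever its cause. The endpoints for supplemental oxygen, ventilation and ITU admission carry no attribution wording. Treatment-related endpoint components must be reported as SAEs. These make serious events visible, but they do not replace an all-cause hospitalisation comparison.

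Three stronger readings are tempting, and the documents do not support them:
- A reader might infer that sites can keep stays from the panel by calling them unrelated, because III-4 speaks of adjudicating COVID-related stays. Both sections have the panel itself decide relatedness, so this is an ambiguity and not a stated filter.
- A reader might take section II-5-1 as saying that respiratory worsening after plasma cannot be told from disease. It reports worsening that "early after CCP transfusion and without evidence of circulatory overload has been observed in several immunosuppressed patients", but these were inpatients with severe disease. It expects lesser risk at an earlier stage and says nothing about distinguishability.
- A reader might take 1.3% as the expected bias. It covers all severe or serious transfusion-related events. Each would have to cause an overnight stay, be non-fatal, be ruled unrelated, and occur in a patient with no other qualifying event.

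**Conclusion.** The point stands as an inconsistency with a one-directional but probably small effect. III-4 and VIII-2 disagree on the panel's blinding. What VIII-2 retains could unmask plasma files and lead to ambiguous, non-fatal respiratory admissions being discounted in that arm alone. Independently, genuine plasma-related admissions fall outside the endpoint, and no listed efficacy analysis shows them.

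The ceiling is about 2 of 170 plasma patients per cohort. At the planned 30% risk this is minor: apparent RR 0.96, with the error favouring plasma at 4.5% instead of 2.5%. It matters mainly if the event rate is far lower, a possibility the protocol leaves open in section X-2 when it calls the real risk considerably uncertain. These figures assume that every event at the top of the cited range is lost. They do not separate loss through unmasking from loss through the endpoint definition, and at r = 0 there is no bias. The documents do not support a claim that the primary result would be seriously distorted.

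**What to change.** 1. Make III-4 and VIII-2 state the same degree of blinding and the same content of the panel's file.
2. Remove references to plasma and transfusion, and the term transfusion reaction, from the files. Keep symptoms, signs, oxygenation, imaging and the laboratory course.
3. State that every overnight stay up to day 28 goes to the panel, whatever the site's view of its cause.
4. Add a supportive ITT analysis, by cohort, of any-cause overnight hospitalisation or death by day 28. Masking alone would not count admissions truly due to plasma; this analysis would.

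The cost is an amendment of wording, somewhat more redaction, more files for the existing panel, slightly less context for its members, and one extra analysis. Hospitalisation is already recorded at visits to day 28 (Table 3) and through SAE reporting. Treatment, sample size and the primary test do not change.

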## **IX. SAFETY REPORTING**

### **IX-1. Criteria for the evaluation of safety**

#### **IX-1-1. Identified safety data**

- Serious adverse transfusion reactions (SAR) expected:
  - Acute allergic / anaphylactic transfusion reaction: rash, angioedema, bronchospasm, hypotension;
  - Transfusion associated acute lung insufficiency (TRALI);
  - Transfusion associated respiratory overload, sudden worsening in respiratory status, acute lung injury, transfusion related dyspnea
  - Acute clinical haemolysis, defined as fall in haemoglobin plus one or more of the following: rise in lactate dehydrogenase (LDH), rise in bilirubin, positive direct antiglobulin test (DAT), or positive crossmatch;
  - Transfusion transmitted infection: bacterial, viral or fungal;
  - Temperature  $>39^{\circ}\text{C}$  or  $\geq 2^{\circ}\text{C}$  rise above baseline;
  - Post-transfusion purpura
  - Sudden hypotension : leading to shock, sudden drop in systolic blood pressure of  $\geq 30$  mmHg with systolic blood pressure  $\leq 80$  mmHg or requiring urgent medical attention
- Serious adverse events (SAE) expected:

As the convalescent plasma will be used as a therapy, the patients could experience the following COVID complications:

- Hospitalisation for progressive COVID-19
- Death for progressive COVID-19

#### **IX-1-2. Regulatory definitions.**

- **Definition of an Adverse Event**

Any harmful manifestation occurring in a person who lends itself to research involving the human person, whether or not this manifestation is related to research or to the investigational drug (s) on the subject (s) of this research.

If an adverse event consists of several signs or symptoms that may be represented by a single syndrome or a diagnosis, the syndrome or diagnosis will be recorded in the observation book as an adverse event, replacing the individual signs and symptoms.

Any event occurring after the signing of the consent and until the end of the subject's participation in the study will be considered as an adverse event.

Signs, symptoms, syndromes or diagnoses present at the time of signing the consent will be considered adverse events if they deteriorate after signing the consent.

- **Definition of a Serious Adverse Event (SAE)**

SAE is an AE that, at any time and any dose, fulfills one or more of the following criteria:

- **Results in death,**
- **Is life threatening,** i.e. the patient was at immediate risk of death at the time of the event; it does not refer to an event which might have caused death if it was more severe,
- **Requires in-patient hospitalization or prolongation of existing hospitalization,** i.e. hospitalization signifies that the patient has been detained, usually involving at least an overnight stay,
- **Results in persistent or significant disability/incapacity,** i.e. substantial disruption of a person's ability to carry out normal life functions,
- **Is a congenital anomaly/birth defect,**
- **Is any important medical event** that may not be immediately life threatening or result in death or hospitalization but, based upon appropriate medical judgment, may endanger the patient or may require intervention to prevent one of the other outcomes listed in the definition above.
- **Suspected transmission of an infectious agent** (e.g., pathogenic or nonpathogenic) via the study drug is considered a SAE.

Any component of a study endpoint that is considered related to study therapy should be reported as an SAE (e.g., death is an endpoint, if death occurred due to anaphylaxis, anaphylaxis must be reported).

a) Death

SAE/SAR resulting in death should be fully documented and reported, even if death occurs after discontinuation of treatment, regardless of the causal relationship between the death and the product under study. If the cause cannot be determined, the death will be considered unexplained.

b) Life-threatening event

This does not apply to adverse reactions which, in a more severe form, could have resulted in death.

c) Disability

A substantial disruption in a person's ability to lead a normal life.

d) Hospitalisation

Certain circumstances requiring hospitalisation do not fall under the seriousness criterion: "hospitalisation/prolongation of hospitalisation" such as:

- Admission for social or administrative reasons;
- Hospitalization predefined by the protocol;
- Hospitalization for medical or surgical treatment scheduled before the research;
- The passage in the day hospital;
- A visit to the emergency room or other hospital department, that does not result in admission (unless considered an important medical or life-threatening event);
- Routine health assessment requiring admission for baseline/trending of health status (eg, routine colonoscopy)

e) Special cases:

Any pregnancy that begins or becomes apparent during the study must be notified to the Sponsor without delay via the pregnancy declaration form, even if the mother is the spouse of the exposed patient (paternal exposure).

The investigator should follow the patient until the pregnancy is terminated or terminated and notify the Sponsor of the outcome.

If the outcome of the pregnancy falls within the scope of the definition of serious adverse events (spontaneous abortion with hospitalization, foetal death, congenital anomaly, etc.) the investigator must follow the procedure for reporting SAEs.

If this is a paternal exposure, the investigator must obtain the consent of the parturient to collect information about the pregnancy.

- **Definition of a serious adverse transfusion reaction (SAR) of an investigational medicinal product**

Any harmful and unwanted reaction in a donor or recipient associated with the administration of blood or blood component.

- **Definition of a serious incident**

Any incident or error susceptible to affect the safety or the quality of blood or blood component and to cause adverse effects. It can be related to any step of the blood transfusion chain : blood collection, biological qualification of the blood donation, preparation, conservation, transport, distribution, dispensation, realization of pre-transfusion analyses, use of labile blood product, delay or lack of their transfusion.

Dysfunctions related to information systems and to patients identification are also incidents if they are susceptible to affect the products' safety or quality and to cause adverse reactions.

An incident is qualified as serious when susceptible to cause serious adverse effects.

- **Definition of an Unexpected Adverse Event**

Unexpected side effect is any side effect of the product, nature, severity, frequency or course of which does not agree with the reference safety information given in the summary of product characteristics or in the investigator brochure for the product when the product is not authorized (see chapter IX Undesirable effects).

- **Definition of a new fact**

Any new data that may lead to a reassessment of the ratio of benefits and risks of the research or of the product being researched, to modifications in the use of this product, in the conduct of research, or of documents relating to the research, or to suspend or interrupt or modify the research protocol or similar research.

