### **Safety analysis of intervention**

Safety endpoints include the following:

- Number of serious Adverse Events at 72 hours after randomisation (Grade 3/4 adverse events and AE unexpected for their nature, onset, evolution, severity or frequency)
- Arterial and venous thromboembolic events at 28, 90 and 180 days after randomization

Adverse events and their characteristics will be described using numbers and percentages per treatment arm. The proportion of participants with each of the reported events, as well as the

proportions of participants with at least one SAE will be compared using Fisher's exact tests. The total number of AE/SAEs and SAEs will also be described for each arm, and compared using Poisson models (with a robust error variance if necessary).

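### The SAE rules need one reading for COVID-19 hospitalisations and deaths, and the pooled between-arm SAE comparison should be shown without primary-endpoint events

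*Protocol*

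**What the plan says.** Section IX-1-1 lists "Hospitalisation for progressive COVID-19", and death from the same cause, among the expected serious adverse events. Section IX-1-2 defines an adverse event "whether or not this manifestation is related to research or to the investigational drug" and counts it as serious if it results in death or "Requires in-patient hospitalization or prolongation of existing hospitalization". Its paragraph on death asks for full reporting of fatal events "regardless of the causal relationship between the death and the product under study". Its list of admissions that do not count as serious does not mention COVID-19.

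The SAE definition ends with a further rule: "Any component of a study endpoint that is considered related to study therapy should be reported as an SAE". The example attached to it is that "if death occurred due to anaphylaxis, anaphylaxis must be reported".

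Section X-3 (safety analysis) lists the endpoint as "Number of serious Adverse Events at 72 hours after randomisation". It then says that the "proportions of participants with at least one SAE will be compared" by Fisher's exact test, and that total counts are compared by Poisson models. Those sentences state neither a window nor how primary-endpoint events are treated. The same paragraph also plans a Fisher comparison for each reported event separately.

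**The concern.** The primary endpoint is an overnight hospital stay for progressive COVID-19, or death, by day 28. On the explicit definitions, every such event is also an SAE. The closing sentence of the definition adds nothing if that is so. Some sites could therefore take it to mean that endpoint events are reported as SAEs only when judged related to plasma.

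On the explicit reading, the pooled SAE comparison carries the efficacy effect inside it. If plasma prevents admissions, its SAE count falls for that reason alone, and serious events caused by transfusion are offset in the total. A reader of the pooled table could conclude that plasma is as safe as standard care, or safer, when the table mainly restates efficacy.

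**Working it through.** **Inputs from the protocol (X-2).** Endpoint rates 0.30 (control) and 0.15 (plasma); two-sided Z-test at 0.05; 90% power; 158 per arm, raised to 170.

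**Planning figure.** With unpooled variance, n = (1.960 + 1.282)² × (0.30×0.70 + 0.15×0.85) / 0.15² = 157.6, so 158 per arm. The figure reproduces.

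**Assumptions, not in the protocol.** SAEs other than endpoint events occur in 5% of controls and 10% of plasma patients (a 5-point harm), independently of endpoint events. A share f of day-28 endpoint events enters the SAE comparison.
- f = 1: SAEs are counted to day 28 or later.
- f = 0.5: an intermediate value.
- f = 0.16: a rough early share, relevant if the 72-hour window governs. It comes from the reference trial in II-3-3, where 6 patients had an endpoint event before infusion, against 13 + 25 = 38 events in all (6/38 = 0.158).
- f = 0: endpoint events are excluded.

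**Formulas.** Control: 1 − (1 − 0.30f)(0.95). Plasma: 1 − (1 − 0.15f)(0.90). For f = 1 these give 1 − 0.70×0.95 = 0.335 and 1 − 0.85×0.90 = 0.235.

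The probabilities below come from exact binomial enumeration of the two-sided Fisher test with 170 per arm.

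| Share f counted | Control | Plasma | Significant in favour of plasma | Significant excess on plasma |
|---|---|---|---|---|
| 1 | 33.5% | 23.5% | 49% | about 0 |
| 0.5 | 19.3% | 16.8% | 7% | under 1% |
| 0.16 | 9.6% | 12.2% | under 1% | 9% |
| 0 | 5.0% | 10.0% | about 0 | 34% |

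**Second case (2% background, 3-point harm).** Fisher's test favours plasma 70%, 18% and 1% of the time for f = 1, 0.5 and 0.16. Detection of the harm is 22% with endpoint events excluded and 2% at f = 0.16.

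**Break-even.** The arms look equal when the proportion of plasma patients with a plasma-caused SAE reaches 1 − (1 − 0.30f)/(1 − 0.15f). For f = 1 this is 1 − 0.70/0.85 = 17.6%. It is 8.1% at f = 0.5 and 2.5% at f = 0.16. The background rate cancels.

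**The case against.** Four points can be made on the other side.

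- **There is no written exemption.** The explicit text says these events are SAEs. The closing sentence of the definition says what to do when an endpoint component is related; that unrelated ones are exempt is only a negative inference, and for deaths the protocol contradicts it. This stands: the text is ambiguous and does not flatly contradict itself. It still needs settling, because the sentence has no function on the explicit reading.
- **The SAE endpoint is set at 72 hours.** If that governs the Fisher comparison, most endpoint events fall outside it and the direction is no longer reversed in the cases above. This limits the size considerably. However, the sentence planning the comparison gives no window, IX-1-2 counts adverse events to the end of participation, and the table of assessments records them to day 180. At a 16% share, detection of the harm is still much reduced.
- **Harm is visible elsewhere.** X-3 compares each reported event separately, thromboembolic events have their own endpoint, and transfusion reactions are a distinct category. This stands, and it confines the problem to the pooled SAE analysis.
- **Detail may sit in documents not shown.** Adverse-event procedures are referred to an appendix, and a fuller analysis plan is promised. Neither removes the ambiguity in the protocol body.

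A reader might also infer that the related-only reading would load COVID-19 endpoint events onto the plasma arm. The documents do not support that. The anaphylaxis example asks for the causal reaction to be reported, and that is genuine plasma harm. Open-label judgement of relatedness could inflate the plasma count, since controls receive no study product, but the effect is modest. If 2%, 5%, 10% or 20% (assumed) of the 170 × 0.15 = 25.5 plasma-arm events were judged related, 0.5, 1.3, 2.6 or 5.1 SAEs would be added. With a 2% background, the chance of a significant plasma excess would be 1%, 3%, 6% or 21%.

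**Conclusion.** The point holds as an ambiguity in the recording rule combined with an SAE comparison that does not separate endpoint events. On the explicit text, primary-endpoint events enter the pooled Fisher and Poisson comparisons, so effective plasma can mask transfusion harm there. Masking is strong if SAEs are counted to day 28 and much weaker if the 72-hour window governs.

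These sizes rest on the planning effect being real, on assumed background and harm rates, on independence of the two kinds of event, and on an early share taken from another trial. It would go too far to say that the planned safety analysis cannot show plasma harm at all, because the event-by-event comparisons remain. The primary analysis is not affected.

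**What to change.** 1. In IX-1-1 and IX-1-2, reconcile the passages into one rule: state whether COVID-19 hospitalisations and deaths are recorded as SAEs, and apply the rule identically in both arms whatever the judged causality. Reword the endpoint-component sentence so that it only asks for the causal reaction to be named as well.
2. In X-3, state the window for the SAE comparison.
3. In X-3, compare SAEs between arms both excluding panel-adjudicated primary-endpoint events and including them, with transfusion reactions listed separately.
4. Align X-1-3, which limits the safety analyses to plasma recipients, with these comparisons by arm.

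The cost is wording and one extra table; the adjudication panel already classifies the hospitalisations. The drawback is that a transfusion-related admission misclassified as COVID-19 would appear only in the all-SAE table, so that table should be kept.
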